## Abstract

**Introduction:**

Cardiovascular events are a major cause of mortality following successful kidney transplantation.

Arteriovenous fistulas (AVFs) are considered the best option for haemodialysis, but may contribute to this excess mortality because they promote adverse cardiac remodelling and ventricular hypertrophy. This raises the question whether recipients with a well-functioning kidney transplant should undergo elective AVF ligation.

**Methods and analysis:**

The COBALT feasibility study is a multicentre interventional randomised controlled trial (RCT) that will randomise renal transplant patients with stable graft function and a working AVF on a 1:1 basis to standard care (continued conservative management) or to AVF ligation. All patients will perform cardiopulmonary exercise testing (CPET) on recruitment and 6 months later. Daily functioning and quality of life will be additionally assessed by questionnaire completion and objective measure of physical activity. The primary outcome—the proportion of approached patients who complete the study (incorporating rates of consent, receipt of allocated intervention and completion of both CPETs without withdrawal)—will determine progression to a full-scale RCT. Design of the proposed RCT will be informed by an embedded qualitative assessment of participant and healthcare professional involvement.

**Ethics and dissemination:**

This study has been approved by the East Midlands—Derby Research Ethics Committee (22/EM/0002) and the Health Research Authority. The results of this work will be disseminated academically through presentation at national and international renal meetings and via open access, peer-reviewed outputs. Existing networks of renal patient groups will also be used to disseminate the study findings to other key stakeholders.

**Trial registration number:**

ISRCTN49033491.

STRENGTHS AND LIMITATIONS OF THIS STUDYThis study will undertake a gold-standard assessment of cardiorespiratory fitness following arteriovenous fistula (AVF) ligation, with the correlate to daily activity levels provided by continuous monitoring via wearable devices.The inclusion of quality of life evaluation will ensure the trial is patient centred, with its outcomes immediately relevant to transplant recipients.The qualitative component will involve patient participants as well as assess barriers to recruitment among healthcare professionals.This feasibility study is a cost-effective and pragmatic approach to demonstrating that the proposed full-scale randomised controlled trial (RCT) is achievable and will likely inform further modifications of the RCT design to ensure its successful delivery.The relatively small numbers required for the feasibility study will limit the ability to identify a threshold value for fistula flow rate that discriminates ‘high-flow’ from ‘low-flow’ states.

## Introduction

For most people with kidney failure, transplantation is the best form of treatment, and offers clear survival, quality of life (QoL) and cost benefits over the alternative option of continued dialysis.^1–4^ Reflecting this, there are now 41 000 people in the UK with a working kidney transplant, which is more than are currently receiving dialysis.^5^ Nevertheless, when compared with the age-matched general population, life expectancy with a working transplant remains poorer,^6 7^ with the incidence of cardiovascular disease in kidney transplant patients almost five times greater than the age-matched general population.^8^ Consequently, recipient death with a functioning graft is now the most common cause of graft loss.^9^ The underlying conditions responsible for renal disease (most notably diabetes or hypertension) have well-documented cardiac sequelae, and additional transplant-specific factors (such as the metabolic consequences of immunosuppression) also increase cardiovascular risk. However, arteriovenous fistulas (AVFs) that are created for dialysis access prior to transplantation may also have profound, and long-lasting, haemodynamic consequences, and thus may contribute to long-term cardiac mortality in kidney transplant recipients.

AVFs are the optimal vascular access for providing haemodialysis for patients with end-stage renal disease (ESRD). Compared with the alternatives; either a central venous catheter or a synthetic arteriovenous graft; AVFs last longer and are associated with improved QoL^10 11^ and a lower incidence of sepsis-related deaths.^12 13^ UK Renal Association guidelines accordingly recommend AVFs as first choice for haemodialysis access.^14^

Nevertheless, AVFs have profound haemodynamic consequences. As an AVF ‘matures’ and the vein enlarges, the blood flow through it increases tremendously, and flows of 2–3 litres/minute are not uncommon.^15^ The drop in systemic vascular resistance triggers neurohormonal responses that increase cardiac contractility and circulating volume, leading to increased ventricular preload, stroke volume and cardiac output. This results in left ventricular (LV) hypertrophy and dilatation, and in severe cases may cause high-output cardiac failure.^16–18^ Even for relatively fit individuals, the cardiac remodelling that occurs following AVF formation likely increases their cardiovascular risk.^19 20^

There is increasing evidence that AVF disconnection improves cardiac structure in stable renal transplant recipients.^21^ It is however not yet clear if doing so will reduce their cardiovascular disease burden. The only randomised controlled trial (RCT) to date^22^ examines the impact of AVF ligation on LV mass using cardiac MRI, and although noteworthy, has its limitations as LV mass is not necessarily reflective of functional capacity, and it has as yet not engendered a change in clinical practice. This is also reflected in the attitudes of transplant patients and their clinicians who often hold strong views about whether their AVF should be preserved or ligated. Stronger evidence is therefore required to guide patient choice and to determine whether fistula disconnection should become standard care following transplantation.

Cardiorespiratory fitness (as objectively measured by cardiopulmonary exercise testing (CPET)) provides a more accurate assessment of functional capacity than imaging studies such as cardiac MRI,^23^ and is a strong independent predictor of both cardiovascular risk and all-cause mortality in various patient groups, including those with ESRD.^24–29^ Peak oxygen uptake (VO_2_, the principal CPET index) and its percentage predicted for age, sex and weight, is the gold standard to objectively assess functional limitations, with small improvements in peak VO_2_ conferring a dramatic reduction in risk of cardiovascular death.^30^ Importantly, QoL correlates with peak VO_2_ for a variety of cardiac diseases,^31–33^ and for the individual, increases in peak VO_2_ improve functional ability and QoL.^34–36^

By combining rigorous assessment of cardiorespiratory fitness with activity monitoring and QoL assessment, we aim to objectively detail how AVF disconnection changes the individual’s physical capacity and assess its impact on their general well-being. The feasibility study detailed in this protocol represents the first step in achieving this goal.

## Objectives

To conduct a feasibility study involving six centres, that mirrors a proposed full-scale RCT, with predefined cut-offs with regards patient recruitment and retention rates to justify progression to the larger RCT.To understand patients’ and healthcare professionals’ perceived acceptability of the proposed trial design and processes.To assess feasibility and acceptability of CPET in the kidney transplant population, as judged by the proportion of participants who successfully complete both tests.To assess patient compliance with wearing a wrist-worn accelerometer (physical activity measurement).

Our longer term objective is to use the findings regarding recruitment and retention from this feasibility study to inform the design and powering of a future multicentre RCT that will test the hypothesis:

In stable renal transplant patients, fistula disconnection improves cardiorespiratory fitness, thereby increasing patients’ activity levels and improving QoL.

## Methods and analysis

### Study design

This interventional, multicentre feasibility study will randomise 40 patients in a 1:1 ratio to the intervention (fistula ligation) or to continued standard care (observance of fistula, with intervention only when clinically indicated), stratified by the fistula site (wrist or elbow) and the binary variable fistula flow rate (high or low). The overall study design is outlined in figure 1.

**Figure 1 F1:**
[figure not shown]
Overall design of Cardiorespiratory Optimisation By Arteriovenous fistula Ligation after renal Transplantation study. AVF, arteriovenous fistula; CPET, cardiopulmonary exercise test; NT pro-BNP, N-terminal pro-B-type natriuretic peptide; SF-36, Short Form 36; VASQoL, Vascular Access Specific Quality of Life.

### Study setting

The study will take place in six NHS hospitals with a vascular access service in England and Scotland: Addenbrooke’s Hospital, Cambridge; Royal Free Hospital, London; Queen Elizabeth University Hospital, Glasgow; John Radcliffe Hospital & Churchill Hospitals, Oxford; University Hospital, Coventry; Freeman Hospital, Newcastle. The study will run from 1 September 2021 until 31 July 2023, with recruitment taking place between 1 March 2022 until 30 November 2022.

### Sample selection

Participants will be considered eligible for enrolment if they fulfil the inclusion and exclusion criteria detailed below. Eligible transplant recipients will be identified by the local clinical team and approached either at their routine transplant follow-up clinic appointment or by post, with full details of the trial procedures and assessments provided at the initial screening visit. At this stage, consenting patients, as well as a small number who decline to take part in the trial, will also be invited to additionally participate in qualitative interviews exploring barriers to recruitment; this will not be a mandatory requirement for trial participation. Identifying and approaching healthcare professionals to participate in qualitative interviews will be the responsibility of the qualitative research team, drawing on their own observations from site visits and communications with the research team. Informed written consent will be obtained from all trial participants (online supplemental files).

10.1136/bmjopen-2022-067668.supp1Supplementary data

10.1136/bmjopen-2022-067668.supp2Supplementary data

### Participant eligibility

#### Inclusion criteria

Kidney transplant recipient aged 16 years or older.At least 1 year from kidney transplantation and with a patent AVF.Stable graft function (eGFR>35 mL/min/1.73 m^2^ (calculated by the Chronic Kidney Disease Epidemiology Collaboration (CKD-EPI)estimation^37^) and without recent rejection episode or recent decline in graft function).Adequate English to understand the study information by verbal explanation and the written participant information sheet.Capacity to provide full informed consent.

#### Exclusion criteria

Patients lacking capacity.Those in whom CPET is contraindicated, as per national guidanceThose considered to have no further first-line options for AVF creation at their wrist or elbow, as assessed by a vascular access specialist.Patients in whom AVF disconnection is indicated on clinical grounds.

### Intervention

This trial will have one standard care control arm and one intervention arm, as described below.

#### Control: standard care

This will involve continued conservative management, with fistula disconnection only performed if clinically indicated.

#### Intervention: fistula disconnection surgery

This comprises either surgical division and oversewing of the fistula vein at the site of the original anastomosis on the artery, or disconnection of the fistula vein entirely from the artery at the anastomotic site. The operation may also include excision of the venous outflow segment if particularly enlarged or aneurysmal. The procedure may be performed under local, regional, or general anaesthesia, typically as a day case.

### Outcomes

For this feasibility study, the primary outcome measure will be the proportion of approached patients who complete the study, defined as the proportion of eligible approached patients that consent, receive the allocated intervention, and complete both CPET tests without withdrawing.

Secondary outcomes are subdivided into: those related to the feasibility of the study; clinical measures that will be measured at baseline and 6 months following intervention, and the differences in these values; and safety outcome measures occurring between study consent and the 6-month assessment visit.

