#### Clinical outcome measures

Peak VO_2_ as measured during incremental CPET on a cycle ergometer.Physical functioning domain score of Short Form-36 Quality of Life questionnaire.^38^Activity levels (mean daily Euclidean norm minus one) as calculated from accelerometry data collected from provided wrist-worn accelerometer device over 7-day period at baseline and following 6-month assessment.Serum N-terminal pro B-type natriuretic peptide value.Office blood pressure.Additional CPET indices: ventilatory anaerobic threshold, endurance time, peak workload, O_2_ pulse, VO_2_/work rate slope (VO_2_/WR), minute ventilation/CO_2_ output slope (VE/VCO_2_), heart rate/VO_2_ slope (HR/VO_2_), perceived exertion rating (Borg scale).Additional domain scores of the Short Form-36 QoL questionnaire^38^: physical role limitation, emotional role limitation, energy/ fatigue, emotional well-being, social functioning, pain, general health, perceived health change.Kidney transplant function (eGFR by CKD-EPI estimation^37^).Fistula-related symptoms reported in modified Vascular Access Specific QoL questionnaire^39^ (for all participants at enrolment, and at 6 months for cohort randomised to standard care).Proportion of participants with at least one major adverse cardiovascular event (MACE)^40^: cardiovascular death; ischaemic cardiovascular event (myocardial infarction, percutaneous coronary intervention, coronary artery bypass graft); hospitalisation for heart failure at any time during the 6-month study period.

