### Progression to full-scale RCT

This feasibility study aims to test the processes of a proposed future multicentre RCT and therefore we will use a traffic-light approach to determine trial progression according to the following indices:

Patient participation:Green: > 40% of approached patients consent to trial participation.Amber: Between 30% and 40% of approached patients consent.Red: < 30% of patients consent.Adherence to randomisation and study completion:Green: > 85% of enrolled participants received the allocated intervention and completed both CPETs without withdrawing.Amber: Between 75% and 85% completion rate.Red: < 75% completion rate.

We anticipate that a green light for the above indices will realise patient recruitment and retention rates within a future full-scale RCT to enable scheduled completion. In response to an amber trigger, the Trial Management Group (TMG) will develop strategies that specifically respond to potential issues with patient participation that have been highlighted by the qualitative analysis. We would not proceed to a full-scale trial if a red signal is triggered.

During this feasibility study, we expect that, once open, each of the participating centres recruits a minimum of one patient per month and that fistula disconnection is performed within 62 days of CPET. If not met, the TMG will attempt to identify and address systematic problems that may hinder the main RCT.

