### Randomisation

Randomisation of consenting participants will be stratified according to fistula site (wrist or elbow) and fistula volume flow (low or high), as determined by a pre-randomisation Doppler ultrasound of the fistula, and allocated in a 1:1 ratio to the intervention (surgical disconnection of fistula) or to standard care (continued conservative management) using an interactive web response system provided by Sealed Envelope. Fistula flow rate will be measured during baseline assessment visits and categorised as either low flow (wrist AVF: ≤800 mL/min, elbow AVF: ≤1400 mL/min) or high flow (wrist AVF: >800 mL/min, elbow AVF: >1400 mL/min). The research team will confirm to the clinical and surgical teams which arm of the trial the participant has been randomised to, with the intervention being performed by a vascular access/transplant surgeon within 62 days of completion of baseline assessments. Given the surgical nature of the intervention, there will be no blinding in this trial with all participants, clinical and research team members aware of which trial arm is assigned at randomisation.

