### Statistical methods

The analysis of the primary outcome of the proportion of approached patients who complete the study successfully will include the proportion of eligible approached patients who consented, received the allocated intervention, completed both CPET tests and did not withdraw, with 95% CIs. As part of the intention-to-treat approach, those who have graft failure, die, or are lost to follow-up will be included in the analysis of the primary outcome as not completing the study successfully. The component proportions and the corresponding 95% CIs of the primary outcome will be presented as secondary outcomes.

The secondary feasibility outcomes of recruitment rate by trial site and the proportion of participants who were compliant with wearing wrist accelerometers, and their 95% CIs, will also be presented. Compliance to wearing the monitor will be assessed by measuring wear time. The days from providing consent to first CPET and the days from CPET to fistula disconnection will be summarised, and the median and IQR presented. Patient and healthcare professional perceived acceptability of the trial design and processes will be analysed using qualitative analysis.

Descriptive statistics of the secondary clinical outcomes will be presented for each arm separately, at baseline, the 6-month assessment, and the average change over time, with 95% CIs. Peak VO_2_ will also be presented by fistula site and according to prespecified flow rate categories. Very limited hypothesis testing will be conducted but mixed linear regression will be used to examine any difference in peak VO_2_ at 6 months between the two treatment arms, with adjustment for fistula site, flow rate, baseline peak VO_2_ and centre. Fistula-related symptoms will be assessed using the modified VASQoL questionnaire for all participants at enrolment and at 6 months for the standard care arm and compared where applicable. The proportion of participants who experienced at least one MACE by 6 months will be presented (alongside 95% CIs), and details of all reported MACEs listed. In addition, summaries of all secondary safety outcomes will be presented by arm.

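### The second assessment is timed from recruitment in one place and from the intervention in another, with no stated origin for controls, so by-arm comparisons at 6 months may not be like for like

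*Protocol article*

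**What the plan says.** All references are to the protocol article.

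- **Visit timing, abstract (Methods and analysis):** "All patients will perform cardiopulmonary exercise testing (CPET) on recruitment and 6 months later".
- **Visit timing, Outcomes:** "clinical measures that will be measured at baseline and 6 months following intervention". Peak VO2 is among these measures. The Intervention section defines the intervention as fistula disconnection surgery. The control section schedules no procedure.
- **Safety window, Outcomes:** "safety outcome measures occurring between study consent and the 6-month assessment visit".
- **MACE window:** the Clinical outcome measures list ends its definition with "hospitalisation for heart failure at any time during the 6-month study period". Statistical methods says "The proportion of participants who experienced at least one MACE by 6 months will be presented". Neither gives a start.
- **Interval to surgery:** Randomisation puts surgery "within 62 days of completion of baseline assessments". Progression to full-scale RCT expects that "fistula disconnection is performed within 62 days of CPET".
- **Calendar, Study setting:** "The study will run from 1 September 2021 until 31 July 2023", with recruitment closing on 30 November 2022. Accelerometry is collected for 7 days at baseline and again after the 6-month assessment.
- **Analysis, Statistical methods:** peak VO2 at 6 months is compared between arms by mixed linear regression, and safety outcomes are summarised by arm. Person-time is not mentioned.

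**The concern.** The abstract and the Outcomes section can both hold only if surgery takes place at recruitment, and the article allows a wait of up to 62 days. A site that follows the Outcomes section also has no date from which to count for a control.

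Whichever way the conflict is settled, something differs between or within arms. Timing from surgery in one arm and from baseline in the other gives the ligation arm longer follow-up. The safety window closes at the 6-month visit, so it lengthens as well. More hospital days, deaths or graft failures would then be expected after ligation even if the underlying rates were equal, and peak VO2 would be compared at different times since baseline. Timing from recruitment in both arms removes that problem, but time since surgery at the second test then varies with the surgical wait.

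The article says that the feasibility study mirrors the proposed full trial, so an unclear clock would be carried forward.

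**Working it through.** The article gives no follow-up length to reproduce. Its one computed figure, the 95% CI for 85% completion in 40 patients, is reproduced by the exact Clopper-Pearson interval for 34/40 (70.2 to 94.3). It does not bear on this point.

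**Inputs.** Six months is taken as 365.25/2 = 182.6 days. The wait from baseline to surgery, w, is 0 to 62 days (Randomisation section).

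**Reading A: ligation timed from surgery, controls from baseline.**
- Ligation, baseline to second visit: 182.6 + w, that is 182.6 to 244.6 days. Controls: 182.6 days.
- Ratio at w = 62: 244.6/182.6 = 1.34. Ratio at w = 31: 213.6/182.6 = 1.17.

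**Safety window under Reading A.** The window opens at consent, so the consent-to-baseline time c is added to both arms and the ratio at w = 62 is (c + 244.6)/(c + 182.6). The article does not give c, so these values are assumptions:
- c = 0: 1.34
- c = 30 days: 274.6/212.6 = 1.29
- c = 60 days: 304.6/242.6 = 1.26

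**What that could do to event proportions.** The article gives no event rates. With a constant hazard and an assumed risk p over 182.6 days, the risk over 244.6 days is 1 − (1 − p)^1.34:
- p = 5% becomes 6.6%
- p = 10% becomes 13.2%
- p = 20% becomes 25.8%

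These are upper illustrations: they take c = 0 and the full 62-day wait for every ligation patient.

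**Reading B: everyone timed from recruitment.** Follow-up is 182.6 days in both arms. Time since surgery at the second test is 182.6 − w, that is about 121 days (w = 62) to about 183 days (w = 0).

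**Calendar under timing from surgery.** Take a patient who completes baseline on 30 November 2022 and waits 62 days.
- Surgery: 30 November 2022 + 62 days = 31 January 2023.
- Second CPET: + 6 months = 31 July 2023, which is the stated study end date.
- Accelerometry: + 7 days = 7 August 2023, after the end date.

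**The 62-day interval.** One section counts from the CPET and the other from completion of all baseline assessments. Baseline also includes a Doppler scan and accelerometry, so the two starts can be different days.

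**The case against.** The strongest reply is that the 62-day gap needs the Outcomes section to govern one arm and a baseline clock to govern the other, and no sentence says so. The abstract speaks of all patients, which gives equal follow-up. The article also speaks of receiving the allocated intervention in both arms, so timing from the intervention could loosely mean from allocated management. The design figure is not shown, and the full protocol may hold a visit schedule. All of this stands, so the imbalance is possible and not established. The conflict between the two stated timings remains, and it does not depend on anything the article omits.

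Four stronger readings are tempting and are not supported.

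- **A reader might apply the 34% excess to every event outcome.** MACE is described over a 6-month window, which is the same length in both arms. Only its start is unstated.
- **A reader might take 34% as the size for safety events.** That window opens at consent, which lowers the ratio, and 34% also needs every ligation patient to wait the full 62 days. Time before randomisation belongs to neither arm, so it dilutes the comparison without favouring either.
- **A reader might infer that late recruits become non-completers and tip the progression rule, say from 35/40 (87.5%, green) to 34/40 (85%, amber).** The worked patient has the second CPET on 31 July 2023, inside the study dates, and accelerometry is not part of completion. A patient who finished baseline after 30 November could overrun, but the article does not say how long baseline takes.
- **A reader might conclude that timing from surgery is wrong.** Fixing recovery time is defensible for a physiological outcome. The fault is that two timings are stated and controls have no equivalent.

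Scale also counts. This is a 40-patient feasibility study with very limited hypothesis testing, and two of the safety items apply to one arm only.

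**Conclusion.** The point holds as a conflict in the stated time origin, with a conditional imbalance between arms. If ligation is timed from surgery and controls from baseline, ligation follow-up from baseline is 0 to 62 days longer (ratio at most 1.34), and the safety-window ratio is somewhat lower. If all are timed from recruitment, follow-up is equal and time since surgery is about 121 to 183 days. These figures assume that the 62-day limit is met. It is also described as an expectation whose breach prompts review, so longer waits could occur; typical waits may be shorter.

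Peak VO2 at 6 months and the by-arm summaries of hospitalisation, death and graft failure may therefore not be like for like. For MACE the defect is only the missing origin. The calendar overrun affects the last accelerometry data; completer status is not shown to be affected. Severity is moderate: secondary outcomes now, and the design passed on to the full trial.

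**What to change.** 1. Reconcile the abstract and the Outcomes section by stating one time origin for the second assessment in both arms. Randomisation is the natural choice. If 6 months after surgery is kept, assign each control a matched offset at randomisation. In either case, record time since surgery as a descriptor.
2. Count MACE, hospitalisation, death and graft failure from randomisation to one common day in both arms, or report rates per person-time.
3. Reconcile the two starting points of the 62-day interval in the Progression and Randomisation sections.
4. Set the study end so that it covers the last participant's 6-month assessment and the accelerometry week after it.

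The cost is protocol wording and a visit-scheduling rule. With visits fixed from randomisation, time since surgery varies within the ligation arm. With a matched offset, control visits move by some weeks.
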